##### Adherence

***Protocol Deviations.*** After each session, the therapist will complete a short questionnaire to check 1. how many skills and application of these skills were discussed, 2. How many mental imagery exercises were conducted, and 3. ask for the presence of deviations to the protocol in that session.

***Procedure Integrity.*** To ensure the procedures differ in the presence of active components (i.e., CBT skill application and use of mental imagery) all sessions will be video-taped. A questionnaire will be developed that measures the presence and duration of the different components in the therapeutic procedures. This questionnaire will be completed by two independent raters.

##### Diagnosis

The SCID-5-CV (First et al., 2019) will be completed by phone during the recruitment phase.

### Data Analyses

All statistical tests will be two-tailed (significance level alpha .05). Descriptives (means, standard deviations) for all measures will be provided for each condition. All analyses will be intention-to-treat and missing data will not be imputed.

#### Main Analyses

The main analyses will be conducted in Stata. First, to test the direct effects of the different procedures on change in therapy processes and symptoms, differences on the primary and secondary outcomes between conditions (CBTSAP versus active control; CBTSAP versus CBTSAP + mental imagery; active control versus CBTSAP + mental imagery) will be tested using multilevel analysis with maximum likelihood estimation (measurements [Level 1] nested within patients [Level 2] nested within therapists [Level 3]). Because the WOR is only measured at two time points, differences between conditions on the WOR will be tested using a repeated measures ANOVA.

Second, to test whether the effect of the procedures is moderated by individual differences in learning capacity, learning capacity will be added as a moderator in the model. Moderation will be tested by adding learning capacity as a main factor and the interaction between learning capacity and condition to the multilevel regression model. For the WOR, the interaction will be added to the repeated measures ANOVA. Moderation of learning capacity will be tested separately for memory functioning and emotional bias. Memory functioning will be tested separately for each component of memory functioning (i.e., verbal working memory, visual working memory, long-term memory), while controlling for type I error (*p* < .016).

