### Sample Size

Based on a medium effect size, alpha = .05, power =.80, number of experimental conditions = 3, number of repeated measurements = 2 to 4 (G*power (Faul et al., 2007)), a total sample size of 102 to 120 participants would be needed to detect a main effect, and 42 to 57 participants to detect an interaction in a repeated measures ANOVA. Simulation studies suggest 80 to 100 participants to detect an interaction effect between three groups (Shieh, 2019) while simulation studies on multilevel analyses suggest *n* = 80 participants to detect a medium effect size with power =.80 (Aarts et al., 2014). Taking into account 20% drop-out, we aim to include a total of 150 participants.

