#### Primary Outcome: Therapy Processes

##### CBT Skills

CBT skill acquisition will be measured in two different ways. First, before and one week after the therapeutic procedure patients will complete the Ways of Responding (WOR; Barber & DeRubeis, 1992). During the WOR, CBT skills of the participants are tested by asking them to think about themselves in various situations and to tell what they would think and do in such situations. The WOR will reflect the level of CBT skills demonstrated by the patient. Patients will receive three scenarios before treatment and three different scenarios after treatment. Answers to each scenario will be coded into 25 different categories (more categories per answer possible) and given a rating of the overall quality of the response (i.e., the raters’ judgment on how well the response would be in improving mood or adjusting to the individual’s needs, range = 1 (very negatively) to 7 (very positively)). The total score will be composed of the number of responses on positive categories (responses considered consistent with CBT) minus the number of responses on negative categories (depressotypic statements). Interrater reliability showed to be high (ranging from α = .91 to α = .98) and discriminant and convergent validity have been supported (for example: the WOR showed no correlation with a measure of self-control, but was correlated to self-report measure of CBT skills) (Barber & DeRubeis, 2001; Strunk et al., 2014). Second, change in CBT skills during the procedures will be measured using the Behavioral Activation for Depression Scale – short form (BADS-SF) (BA skills) and Cognitive Change Sustained Change (CCSC) (CT skills). The BADS-SF consists of nine items, each rated on a 7-point Likert Scale and internal consistency (α = .81) and construct and predictive validity were supported (for example: the BADS-SF was positively related to measures of reward, negatively related to measures of avoidance and predicted time spent in high and low rewarding behavior; Manos et al., 2011). An example item from the BADS-SF is: ‘There were certain things I needed to do that I didn’t do’. The CCSC consists of 9 items rated on a 7-point Likert scale and internal consistency was supported (α = .93) and the scale showed convergent and discriminant validity by showing a relation with a self-report scale of CBT skills and no relation with a measure of attributional styles (Schmidt et al., 2019). An example item from the CCSC is: ‘I noticed myself thinking less negatively.’

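### Having only two time points is not a reason to test the WOR by repeated measures ANOVA, which uses the baseline inefficiently and leaves patients without a follow-up score out of the contrast

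*Protocol article*

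**What the plan says.** All references are to the protocol article.

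- **Timing of the WOR.** Under CBT Skills: "before and one week after the therapeutic procedure patients will complete the Ways of Responding". Table 1 agrees, marking the WOR at baseline and follow-up only. The two sets of test material differ: "Patients will receive three scenarios before treatment and three different scenarios after treatment".
- **Method for the WOR.** Under Main Analyses: "Because the WOR is only measured at two time points, differences between conditions on the WOR will be tested using a repeated measures ANOVA". The moderation test for the WOR is placed in the same ANOVA.
- **Method for the other primary and secondary outcomes.** Differences between conditions "will be tested using multilevel analysis with maximum likelihood estimation (measurements [Level 1] nested within patients [Level 2] nested within therapists [Level 3"]).
- **Analysis set and missing data.** Under Data Analyses: "All analyses will be intention-to-treat and missing data will not be imputed".
- **Expected loss.** Under Sample Size: "Taking into account 20% drop-out, we aim to include a total of 150 participants".

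The article names no other analysis of the WOR and gives no rule for patients who have no follow-up WOR.

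**The concern.** Three features of the plan combine.

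First, the number of occasions is the only reason given for taking the WOR out of the multilevel model, and it does not support that step. Two occasions are enough for a likelihood-based mixed model. The plan itself shows this: Table 1 lists the BSI, a secondary outcome, at baseline and follow-up only, and Main Analyses exempts the WOR alone.

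Second, with two occasions the condition-by-time test is the same as a one-way ANOVA of change scores. A patient without a follow-up WOR has no change score and, without imputation, adds nothing to it.

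Third, a change score gives the baseline a fixed weight of one, whatever its correlation with follow-up. Baseline adjustment estimates that weight and is never less precise in large samples.

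What is at stake is precision on the one CBT-skill measure based on demonstrated performance; the other two, BADS-SF and CCSC, are rating scales. The moderation test, part of the second main aim, inherits the same choice.

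**Working it through.** **Inputs from the article.** 150 patients, 50 per arm; 20% dropout; two-sided alpha 0.05; three conditions; a medium effect; two WOR occasions.

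**Assumptions.** A medium effect is read as f = 0.25 for three groups and d = 0.5 for a pair. The article gives no pre-post correlation rho for the WOR, so 0.3, 0.5 and 0.7 are shown. Variances are equal at both occasions and set to 1.

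**Step 1: the plan's own figure.** For the between-group effect with m = 2 occasions and rho = 0.5 (assumed, the usual software default), lambda = f² × N × m / (1 + (m − 1) × rho) = 0.0625 × 120 × 2 / 1.5 = 10. The smallest N divisible by three that reaches 80% power is 120. Then 120 / 0.80 = 150, so the stated total reproduces.

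**Step 2: who enters the test.** 0.20 × 150 = 30 patients without a follow-up WOR, leaving 120, or 40 per arm. This treats the planning allowance for dropout as the proportion with no follow-up WOR. In a long-format ANOVA a baseline-only patient may stay in the data set, but contributes nothing to condition-by-time.

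**Step 3: variance.** Change score: 2(1 − rho). Baseline-adjusted: 1 − rho². The ratio of change to adjusted is 2 / (1 + rho).

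| rho | Change | Adjusted | Ratio |
|---|---|---|---|
| 0.3 | 1.40 | 0.91 | 1.54 |
| 0.5 | 1.00 | 0.75 | 1.33 |
| 0.7 | 0.60 | 0.51 | 1.18 |

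**Step 4: power.** The pairwise noncentrality is 0.5 / (SD × √(2/40)), using the noncentral t. At rho = 0.5 it is 0.5 / (1.000 × 0.2236) = 2.24 for change and 0.5 / (0.866 × 0.2236) = 2.58 for the adjusted analysis. The omnibus column is the three-arm F test with f = 0.25 on the follow-up score and N = 120.

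| rho | Pairwise, change vs adjusted | Omnibus, change vs adjusted |
|---|---|---|
| 0.3 | 46% vs 64% | 52% vs 72% |
| 0.5 | 60% vs 72% | 68% vs 81% |
| 0.7 | 81% vs 87% | 89% vs 93% |

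**Step 5: when is there bias?** Simulation with two arms of 50, true difference 0.50, rho = 0.5, about 21% missing follow-up, and logistic dropout on baseline.

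| Dropout depends on baseline | Completer change score | ANCOVA | ML, all patients, baseline free |
|---|---|---|---|
| Same way in both arms | 0.50 | 0.50 | 0.50 |
| Opposite ways by arm (slopes ±1 per SD) | 0.32 | 0.50 | 0.50 |

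Milder differential patterns (slopes 1 and 0, or ±0.5) at rho = 0.5 give a bias of about 0.10 SD.

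**Step 6: what gives the precision?** With the same dropout in both arms, the simulated standard deviation of the estimate was 0.223 for the change score, 0.221 for ML with free baseline means and 0.195 for ANCOVA. Moving to ML therefore protects against the bias in step 5, but the gain in precision comes from adjusting for the baseline or constraining its mean to be equal across arms.

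**The case against.** Repeated measures ANOVA is a recognised and valid test in a randomised trial, and the article openly says that nothing will be imputed. Patients can still be analysed in the arm to which they were assigned. The WOR is one of several primary measures, and two other CBT-skill scales do get the multilevel model. All five therapists deliver all procedures, so a therapist main effect is crossed with condition and leaving that level out probably matters little. These points stand, and they keep the matter to one of efficiency and consistency.

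A reader might infer more than the documents support:

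- **That the baseline is wasted.** It is not: it is the first repeated measure. The change score does worse than ignoring baseline altogether only if rho is below 0.5. The different scenarios before and after may lower rho, but no value is given.
- **That the result will be biased.** This needs dropout that depends on baseline WOR differently by arm. Nothing in the article suggests it: the arms have the same number and length of sessions and the same therapists, over at most five weeks. A bias of 0.10 SD is also under half the standard error of a pairwise contrast at rho = 0.5, which is √(2/40) = 0.22.
- **That the intention-to-treat principle is flatly broken.** The difficulty is the completeness of the analysis set, not the reassignment of patients.
- **That the trial is too small because of this.** The sample size already allows for 120 completers.
- **That ANCOVA would solve everything.** It recovers the precision, but still omits patients without a follow-up WOR.

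**Conclusion.** The point holds as a matter of analysis choice and should be fixed. The stated reason for the ANOVA is not valid and is inconsistent with how the plan treats the BSI. The planned test rests on about 120 of 150 patients, if the 20% allowance describes missing follow-up WOR scores. Its variance is 18% to 54% larger than under baseline adjustment for rho from 0.7 down to 0.3, which costs about 6 to 18 percentage points of pairwise power at d = 0.5. The size depends on a correlation that the article does not give; the direction does not. Bias is a conditional risk, not an expected result.

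**What to change.** Replace the sentence on the WOR in Main Analyses. Analyse the WOR with the maximum-likelihood multilevel model already specified for the other outcomes, including the therapist level. Use all randomised patients with any WOR score, hold the baseline mean equal across arms, and take the condition contrasts at follow-up. Move the WOR moderation test into the same model. State the equal-baseline constraint explicitly, since step 6 shows that the precision depends on it. If ANCOVA on baseline WOR is preferred for simplicity, say that it leaves out patients without a follow-up WOR and reconcile that with the intention-to-treat sentence.

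The cost is about one sentence. Data, visits, software and sample size are unchanged. The change should be made before outcome data are compared by arm, so that it cannot appear data-driven.

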The aims of this randomized trial are two-fold. The first aim is to investigate and compare the direct effects of three procedures (active control, CBT skill acquisition (CBTSAP), CBTSAP + mental imagery) on changes in therapy processes (the acquisition of CBT skills, changes in idiosyncratic dysfunctional thoughts and behaviors, general dysfunctional thinking and reward processing) and depressive symptoms in a sample of patients with a diagnosis of major depressive disorder who do not currently receive other psychological treatment. We expect that compared to an active control procedure, the procedures focused on CBT skill acquisition (CBTSAP and CBTSAP + mental imagery) will lead to more improvement in the therapy processes and depressive symptoms. Second, we will investigate whether the effect of the therapeutic procedures is moderated by individual differences in learning capacity. Learning capacity will be defined as the presence of memory functioning and emotional bias (i.e., where more emotional bias and better memory functioning are defined as better learning capacity). Following earlier literature on the measurement of memory (Unsworth, 2010; Wilhelm et al., 2013), the measurement of memory functioning will be composed of both working memory and long-term memory tasks. We expect that, compared to the active control procedure, better learning capacity will be associated with larger improvements in the therapy processes and depressive symptoms in both the CBTSAP’s. In addition, we expect a difference between CBTSAP with versus without mental imagery: patients with low learning capacity will have most benefit from mental imagery and lower learning capacity will therefore be associated with more improvement in the therapy processes and depressive symptoms in the CBTSAP with mental imagery compared to the CBTSAP without mental imagery condition.

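### The moderation test adds learning capacity by condition without time, so as written it tests average level over all occasions, not improvement

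*Protocol article*

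**What the plan says.** The Background of the protocol article puts the moderation hypothesis in terms of change: compared with the active control, "better learning capacity will be associated with larger improvements in the therapy processes and depressive symptoms" is expected in both CBTSAP arms. The companion hypothesis on mental imagery for patients with low learning capacity is also about improvement.

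Main Analyses introduces the base model as one "to test the direct effects of the different procedures on change in therapy processes and symptoms". It is a multilevel model whose lowest level is the single measurement, within patients, within therapists. Moderation is then tested by "adding learning capacity as a main factor and the interaction between learning capacity and condition to the multilevel regression model". For the two-occasion skills test: "For the WOR, the interaction will be added to the repeated measures ANOVA". The analysis section lists no time term, change score or baseline covariate for these models.

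Two further places fix which rows enter. Main Analyses chooses the repeated measures ANOVA "Because the WOR is only measured at two time points". Table 1 shows those two to be baseline and follow-up, so baseline counts as an outcome occasion. Randomization and Procedure places randomisation after the introduction session. By Table 1, the BADS-SF, CCSC and BDI-II therefore have two pre-randomisation occasions out of six. The WOR, CBI, CCL, RPI and TEPS have one each.

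**The concern.** In a model with one row per measurement, a product of two patient-level variables (arm and baseline learning capacity) is itself a patient-level term. Its coefficient is the between-arm difference in the slope of the patient's average score on learning capacity. Some of the averaged occasions precede randomisation, where no moderated treatment effect can exist. The hypothesis concerns change, which requires either an interaction that also involves time or a post-randomisation outcome conditioned on its earlier value.

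Adding condition by time to the base model would not cure this. If learning capacity enters only through its main effect and its product with condition, the moderation is still forced to be constant over all occasions, including those before randomisation.

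At stake is one of the trial's two main aims, which the Discussion presents as a first. A null moderation result could arise from the model term alone.

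**Working it through.** **The plan's own figure.** The article gives no sample size for moderation by a continuous covariate. Its total does reproduce. The Sample Size section starts from "Based on a medium effect size, alpha = .05, power =.80" with three conditions and 2 to 4 measurements. With f = 0.25 and a correlation of 0.5 (both assumed), a noncentral-F calculation for the between-condition effect needs 120, 108 and 102 patients for 2, 3 and 4 measurements. The condition by time interaction needs 42 with two measurements; 57 is matched with three measurements and a lower-bound sphericity correction of 0.5. Then 120/0.80 = 150. The check below uses 120/3 = 40 completers per arm.

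**Assumptions not in the article.** Unit SD at each occasion, a common within-patient correlation ρ = 0.5, a moderator with unit SD, and a difference between two arms of δ = 0.6 SD of improvement per SD of learning capacity.

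**WOR (one occasion before, one after).**
- As written: effect (0 + δ)/2 = 0.3; variance of the two-occasion mean (1 + ρ)/2 = 0.75; SE = √(2 × 0.75/40) = 0.194; power 34% at .05.
- Follow-up adjusted for baseline: effect 0.6; residual variance 1 − ρ² = 0.75; the same SE of 0.194; power 87%.
- At the article's .016 threshold for the memory components: 20% against 75%.
- Information, as squared effect over variance: 0.25/0.75 = 0.333 as written, 1/[2(1 − ρ)] = 1.0 for the term with time, and 1/0.75 = 1.333 with baseline adjustment. The term as written keeps 0.333/1.333 = 25% of the last.
- Range over ρ: 38% against 80% at ρ = 0.3, and 31% against 96% at ρ = 0.7.

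**Other outcomes.** The share of the follow-up effect that the term recovers is the mean of the effect profile over occasions.

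| Outcome | Assumed profile | Share recovered |
|---|---|---|
| CCL, RPI, TEPS | 0, 1, 1 (sustained) | 2/3 |
| BADS-SF, CCSC, BDI-II | 0, 0, 0, 1/3, 2/3, 1 | 1/3 |
| same | 0, 0, 0, 1, 1, 1 | 1/2 |
| same | 0, 0, 1, 1, 1, 1 | 2/3 |
| CBI | 0, 0, 1, 1, 1, 1 | 2/3 |
| CBI | 0, 1, 1, 1, 1, 1 | 5/6 |

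For the BADS-SF, CCSC and BDI-II, the variance of the six-occasion mean is (1 + 5 × 0.5)/6 = 0.583. Follow-up given the two earlier values has residual variance 1 − 2 × 0.25/1.5 = 0.667, so information 1.5. The three profiles keep (0.111/0.583)/1.5 = 13%, (0.25/0.583)/1.5 = 29% and (0.444/0.583)/1.5 = 51%.

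**Simulation.** 4,000 runs, 40 per arm, ρ = 0.5, moderation of 0.5 SD per SD in both CBTSAP arms and none in control, three-arm F-test, one pre-treatment occasion.

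| Scenario | As written | Linear time interaction | Post-baseline mean adjusted for baseline |
|---|---|---|---|
| 2 occasions | 22–24% | 59% | 71–73% |
| 6 occasions, linear growth | 28% | 76% | 60% |
| 6 occasions, immediate step | 68% | 46% | 96% |
| No moderation | 5% | 5% | 5% |

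The mean coefficient as written was 0.25 to 0.26 with two occasions or linear growth, and 0.42 under the step, against a true 0.50.

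**The case against.** The strongest reply is that this article condenses a fuller plan and does not list the base model's fixed effects. If the outcome were a change score, or post-randomisation values adjusted for baseline, learning capacity by condition would be the right term. With condition by time in the model, the sentence might be shorthand for an interaction with that effect. This stands in part: one cannot infer that the wrong parameter will certainly be estimated. But the article does name the term that tests moderation, puts it in a model of single measurements, and counts the WOR's baseline as an outcome occasion. Followed literally, that does not test the stated hypothesis, so this is more than missing detail.

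For the WOR, some repeated-measures software crosses between-patient terms with time automatically, and the problem may then vanish in practice. The text does not say so, and the multilevel outcomes gain nothing from it.

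Three stronger readings are not supported.
- That dilution is always one-half or worse. Table 1 gives the CCL, RPI and TEPS two post-randomisation occasions out of three. For the six-occasion measures the loss depends on when the effect appears, and Table 1 does not say whether session scores are taken before or after the session.
- That the test is biased or gives false positives. Under randomisation the expected baseline difference is zero, and rejection stayed near 5%. Chance imbalance adds variance only.
- That any interaction with time is better. Under an immediate step, a linear one did worse than the term as written (46% against 68%).

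**Conclusion.** The point holds in this form: the moderation term, as worded, targets a between-arm difference in average level over all occasions, some of them before randomisation, while the hypothesis concerns improvement. The size test remains valid. What suffers is the estimand and, usually, power.

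The dilution factors follow from Table 1 and the assumed course of the effect. They are one-half for the WOR, about two-thirds for a sustained effect on the CCL, RPI and TEPS, and one-third to two-thirds for the BADS-SF, CCSC and BDI-II. The CBI loses least, keeping two-thirds to five-sixths under the profiles shown.

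The power figures rest on an effect size and a correlation that the article does not give, and should be read as illustrations. The WOR comparison keeps its direction over correlations of 0.3 to 0.7. The Discussion already concedes low power for small effects, so the loss matters.

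**What to change.** Replace the moderation sentences with wording such as: moderation will be tested by the interaction of condition and learning capacity on the post-randomisation scores, adjusted for the pre-randomisation value or values. An alternative with the same target is condition by time by learning capacity, with all lower-order terms, time as a categorical factor, and the contrast evaluated at follow-up. A linear slope alone should not be the only coding of time. For the WOR: condition by learning capacity on the follow-up score, adjusted for baseline.

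For the WOR, the baseline-adjusted form is the more precise of the two under the assumptions above (information 1.333 against 1.0). If the base model already works on change or on baseline-adjusted scores, saying so settles the matter.

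The cost is analysis-plan wording only: no new data, visits or patients. The change should be dated before unblinded data are examined.

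### The fixed p < .016 for each of the three memory moderators is valid but less powerful than Holm's step-down rule, which gives the same familywise protection

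*Protocol article*

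**What the plan says.** The Data Analyses section sets the general rule: "All statistical tests will be two-tailed (significance level alpha .05"). Under Main Analyses, the moderation question is divided in two: "Moderation of learning capacity will be tested separately for memory functioning and emotional bias". The memory part is divided again, with a test for "each component of memory functioning (i.e., verbal working memory, visual working memory, long-term memory), while controlling for type I error", and the threshold is given there as p < .016. No multiplicity method is named, but one fixed cut-off for three tests, close to .05/3, is single-step Bonferroni. No adjusted threshold is given for emotional bias.

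The Background section makes moderation the second of the two aims: "Second, we will investigate whether the effect of the therapeutic procedures is moderated by individual differences in learning capacity". It defines better learning capacity by more emotional bias and better memory functioning, and says of the latter that "the measurement of memory functioning will be composed of both working memory and long-term memory tasks".

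**The concern.** The threshold is written into the article, so it is not a detail left to an analysis plan that we cannot see. Each memory component must reach .016 whatever the other two show. If one component is clearly significant and a second has p = .02, the second is declared non-significant. Holm would accept it as the second smallest of the three p-values, because .02 is below .025.

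What is at stake is power for the second and third memory components, once one has been established. Moderation is a main aim. The Sample Size section plans at the unadjusted level ("Based on a medium effect size, alpha = .05, power =.80, number of experimental conditions = 3"), and the Discussion concedes that the trial is underpowered for small effects between the conditions. A more powerful rule with the same error guarantee is therefore worth having.

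**Working it through.** **Inputs from the protocol article.** Two-sided alpha of .05 (Data Analyses); three memory components, each at p < .016 (Main Analyses).

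**Assumptions, because the article gives no figures.** Each true moderator has 80% power at two-sided .05, borrowing the planning target in Sample Size. The correlation among the three test statistics is 0, .3 or .5. Each test is treated as a two-sided z-test.

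**Step 1: the plan's threshold.** .05/3 = .01667, which is .016 when cut to three decimals. The difference is on the conservative side.

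**Step 2: does the plan's rule control the error?** Upper bound: 3 × .016 = .048. If the tests are independent: 1 − (1 − .016)³ = .0472. Without any correction: 1 − .95³ = .1426. The rule does what the article says it is for.

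**Step 3: Holm.** Order the three p-values. Compare the smallest with .05/3 = .0167, the next with .05/2 = .025 and the largest with .05, stopping at the first failure. Every threshold is at least .016, so whatever the fixed rule rejects, Holm rejects too. Familywise error stays at or below .05 under any dependence. This holds for any valid p-values, so it covers both the multilevel models and the ANOVA of the Ways of Responding test.

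**Step 4: power at one test.** 80% power at .05 means a noncentrality of 1.96 + 0.84 = 2.80. Power at .016 is then about 65.3%, and at .0167 about 65.9%.

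**Step 5: simulation, 400,000 replicates per scenario.** Power per true component, in percent:

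| True moderators | Correlation | p < .016 | Holm | Gain (points) |
|---|---|---|---|---|
| 1 | 0 to .5 | 65.3 | 66.0 | 0.7 |
| 2 | 0 | 65.3 | 69.6 | 4.3 |
| 2 | .3 | 65.3 | 69.3 | 4.0 |
| 2 | .5 | 65.3 | 69.0 | 3.7 |
| 3 | 0 | 65.3 | 75.0 | 9.7 |
| 3 | .3 | 65.2 | 74.1 | 8.9 |
| 3 | .5 | 65.3 | 73.6 | 8.3 |

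With one true moderator, about 0.6 of the 0.7 points comes from using .0167 instead of .016, not from stepping down.

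**Step 6: chance of at least one rejection.** Holm and exact Bonferroni (.05/3) are identical in every scenario, since both begin with the same comparison. Against p < .016 the difference is at most 0.6 points. With three true moderators and correlation .3, for example, it is 90.8% versus 91.1%.

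**Step 7: error rates.** With all three null, familywise error was .0430 to .0474 under p < .016 and .0447 to .0493 under Holm. With two true moderators, the one null component is rejected in 1.6% of trials under the fixed rule and in 3.5% to 3.7% under Holm. Holm thus uses more of the error allowance but stays within .05.

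**Step 8: sensitivity to the assumed power.** At correlation .3 with three true moderators, the gain per component is about 8 points if power at .016 is 50% (50% to 58%), and about 6 points if it is 35% (35% to 41%). At 35%, the gains are 3 points with two true moderators and 0.7 points with one.

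**The case against.** The strongest reply is that nothing here is wrong. Bonferroni is pre-specified, widely used and valid, and it delivers the error control the article asks of it. Choosing it over Holm is a matter of efficiency. That stands in full.

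Three stronger readings might be inferred, and the documents support none of them.

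- *That the plan throws away power for its whole second aim.* The .016 applies only to the memory half; emotional bias is tested separately. Within the memory half, Holm cannot help until one component has passed .0167.
- *That the plan hypothesises the case where Holm gains most, with all three components moderating.* The Background states its hypotheses for learning capacity as a whole. It lists the tasks that make up memory functioning, but it neither predicts that each will moderate nor requires all three to be significant. The gain in detecting all three together (35.6% to 55.2% at correlation .3, under the same assumptions) answers a question the article does not set.
- *That the fixed threshold has no advantage.* A single-step rule gives matching simultaneous confidence intervals simply, and a decision on each component that does not depend on the other two.

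It may also be said that moderation is tested on several outcomes, so Holm within one set of three does not control error across the study. That is true, but the .016 rule has the same limit. Holm can be applied to exactly the p-values that the fixed threshold now judges, so the comparison between the two rules is unaffected.

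**Conclusion.** The point holds as an optional, low-cost gain in efficiency. The fixed threshold is valid, but Holm never rejects less and keeps familywise error for the three tests at or below .05. That comparison rests on no assumption about effects.

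The size of the gain does rest on assumptions. With 80% power per true moderator at .05 and correlations of 0 to .5, it is negligible if one component is a real moderator, modest if two are, and material only if all three are. It is smaller if the interaction tests are weaker than assumed. The article gives neither effect sizes for the individual memory moderators nor correlations among them, so it cannot be said which case applies, or that true moderators will in fact be missed. The z-test calculation is also only an approximation for an interaction with a three-level condition.

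**What to change.** In Main Analyses, replace the fixed threshold by: *Holm step-down across the condition-by-component interaction p-values of the three memory components, applied within each outcome, familywise alpha .05 (.0167, .025, .05).* Make the change before any outcome data are analysed and record it as a dated amendment.

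It is one phrase and needs no further patients or data. The costs are simultaneous confidence intervals that are less simple to state, and a decision on each component that depends on the other two tests. If the authors value the simplicity of a single-step rule, .0167 in place of .016 recovers about 0.6 points per true component and leaves the rest of the plan as it is.
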